## Discussion

Although AMKs play and important role in the Netherlands in the attempt to end child maltreatment and to provide the necessary care for maltreated children and their families, the children’s mental health and quality of life after AMK involvement has not yet been studied. This gap in the available knowledge, as well as prior research showing the negative impact of child maltreatment on the mental health and quality of life of children, means there is a need for the present study. The results of this study will primarily provide information on changes in the mental health and quality of life of maltreated children over a period of 1.5 years after an AMK becomes involved. Secondly, the study will explore determinants that positively or negatively influence the mental health and/or quality of life of the maltreated children. These results will help to identify the children that are most vulnerable to developing mental health problems and will define determinants that can be influenced to improve these children’s mental health and quality of life or to prevent additional harm. Thirdly, the results will provide information on the differences in mental health and quality of life outcomes between families of Dutch origin and families originating from Morocco and Suriname.

This study has several strengths. First, this study will be performed among maltreated children and their parents shortly after they have been reported to an AMK, which may reduce recall bias. Since there is a lack of studies examining outcomes shortly after or during the actual maltreatment and outcomes may be expected to be different during or shortly after abuse in comparison with years later, this study can contribute to the knowledge about the short-term effects of maltreatment.

Another strength is the use of child self-reports. Many studies have used proxy informants when collecting data on children’s mental health and quality of life. However, the use of proxies is not always the best option when measuring subjective constructs, and research findings have shown discrepancies between child and parent reports [26-29]. For example, quality of life studies have reported better agreement between child and proxy reports on the physical, more observable, dimensions and poor agreement on the social and emotional, non-observable, quality of life dimensions [26]. As a consequence, the value of obtaining children’s self-reports is increasingly recognized and several studies have examined the accuracy and reliability of child reports. These studies have shown that children can provide reliable and accurate information as informants [26,55,56]. The present study will examine the outcomes of maltreated children aged 5–16 years, using child self-reports as much as possible.

Quality of life has become an important topic of research on the adverse effects of childhood maltreatment, as the concept of quality of life adds a subjective component to objective, clinical measures [11-14]. Self-reported quality of life will be examined as one of the main objectives of this study. This should be useful, as quality of life research focusing on children, especially maltreated children, has so far been scarce [15-17].

This study also has several limitations. First, selection bias cannot be ruled out. Participation is voluntary and families will be recruited shortly after a report of suspected child maltreatment has been filed with an AMK. This can be expected to be a stressful time for most families. In addition, families might be inclined to refuse participation in view of the perceived accusation and/or stigmatization by the child maltreatment report [57]. This may make it harder to find participants for this study, which may lead to a risk of selection bias. To increase the likelihood of success, the researchers will remain in close contact with the participating AMKs during the recruitment process, so they can adjust the process if necessary. In addition, a non-response analysis will be performed to examine the presence of this possible selection bias. Secondly, there is a risk of considerable loss to follow-up. One reason may be that families of maltreated children tend to move more frequently than non-maltreated children and their families [58]. Families may forget to forward their new address and phone number. To minimize loss to follow-up due to changes in contact information, participants will be asked to provide various kinds of contact information. Another possible reason is that many families reported to AMKs are 'multi-problem’ families [59], so there might be new and/or additional problems at follow-up which might cause families to drop out of the study.

To conclude, this study will be the first to provide information on mental health and quality of life outcomes of maltreated children over a 1.5 year period after being reported to an AMK. In addition, it will explore determinants that influence mental health and quality of life outcomes, and will provide information on the influence of ethnicity on maltreatment outcomes. Results will contribute to the knowledge that is required to provide high-quality care to maltreated children.

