### Recruitment and sample size

Parent–child dyads will be recruited from seven AMKs in the Netherlands. All AMKs in the four largest cities (Amsterdam, Rotterdam, The Hague, and Utrecht) will be approached to participate in the recruitment for the study, in view of their high percentage of residents of Moroccan and Suriname origin. An additional three large AMKs will be asked to take part in the recruitment phase of the study, taking the level of urbanization into account, to ensure that the sample is representative of Dutch society. The study will focus on children aged between 5 and 16 years, as approximately 70% of all reports to AMKs concern children in this age range [35]. In addition, the study will focus on reports to AMKs of physical and/or emotional abuse, physical and/or emotional neglect and/or sexual abuse, which account for about 70% of all reports to AMKs [35]. Families that meet the inclusion criteria will be approached by phone by an AMK employee within three months after the report was filed with the AMK. In this phone call, they will provide general information about the study, and will invite one parent and one child per family to participate.

Based on expert opinion, we expect a participation rate of 5%. This low expected rate is due to the delicate subject of the study: participants will be recruited shortly after a suspected child maltreatment report, so people might refuse to participate due to the perceived accusation and/or perceived stigmatization and/or stress because of the report to the AMK. In addition, we are expecting obstacles in the recruitment process, for instance because there is often no phone number in the AMK records, people may not be available when the phone call is made, people may not be able to speak Dutch. If a parent–child dyad is willing to participate, an appointment with a member of the research team will be made at a time and place of the families’ choosing (which in most cases will probably be a home visit). During this visit, prior to starting to complete the questionnaire, parents and children will be asked to give written informed consent for their participation. Parents will also be required to give informed consent for the participation of their child.

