After the baseline assessment, an estimated 40% of the participants are expected to be lost to follow-up. To minimize loss to follow–up, parents and children will be asked to write down various types of contact information on the informed consent form, e.g. both home and mobile phone numbers, and email addresses. If phone numbers are no longer valid at follow-up, an email or letter will be sent to the last known home address with the request to contact the research team. In case of no response, a member of the research team will visit the family at their last known address to check if they have moved.

This study aims to examine differences in outcomes when comparing children from families of Dutch origin with children from families originating from Morocco and Suriname. To prevent numbers that are too small to allow a useful analysis, we will oversample families originating from Morocco and Suriname. To this end, extra time will be invested in reaching these families, even beyond the times of the day when AMK employees would normally make recruitment calls. A separate list with phone numbers of eligible Moroccan and Suriname families will be printed, and a Moroccan AMK employee will call the Moroccan families to minimize the risk of refusal to participate due to a possible language barrier. Overall, we expect about 150 parent–child dyads to be available for the last assessment 1.5 years after the report to the AMK.

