### Analyses

First a non-response analysis, using univariate analysis, will be carried out to compare characteristics of the included participants with the characteristics of the entire population of children aged 5–16 years reported to the seven participating AMKs within the recruitment period of this study. The following characteristics will be studied: age of the child, gender of the child, ethnicity, living situation, type of maltreatment as verified by the AMK, outcome of the AMK procedure.

Missing data at follow-up will be imputed using regression imputation. Prior to the analyses the possible influence of (1) the different AMKs (as families will be derived from 7 AMKs), and (2) the time between the report to the AMK and the completion of the questionnaires will be examined.

The first research question, regarding the mental health and quality of life of maltreated children over a 1.5 year period, will be addressed using a longitudinal multi-level analyses (measurements nested within respondents, i.e. children and parents/caregivers, respectively) to assess changes in mental health and quality of life over time [54]. The second research question, regarding the influence of relevant determinants on the mental health and quality of life of maltreated children, will be addressed by exploring the potential effects of these determinants on the outcome variables by testing the interaction between potential effect modifiers at T0 and the outcome variables at Tf-upx (where 'f-upx’ indicates the successive moments of measurement during follow–up).

To answer the third research question, regarding differences in mental health and quality of life outcomes between children from families of Dutch origin with children from families originating from Morocco and Suriname, 'ethnicity’ will be entered as a covariate in the analysis.

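### With 40% loss expected and new family problems named as a possible cause, regression imputation and a selection check at entry only leave the 1.5-year course open to a bias that nothing in the article would reveal

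*Protocol article*

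**What the plan says.** Four statements in the protocol article bear on this point.

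- **Amount of loss (Recruitment and sample size).** "After the baseline assessment, an estimated 40% of the participants are expected to be lost to follow-up". The same section ends with the yield: "we expect about 150 parent–child dyads to be available for the last assessment 1.5 years after the report to the AMK".
- **Reasons for loss (Discussion, second limitation).** One is residential mobility: "families of maltreated children tend to move more frequently than non-maltreated children and their families". The other concerns multi-problem families, where "there might be new and/or additional problems at follow-up which might cause families to drop out of the study". Both are put as possibilities, and the 40% is not divided between them.
- **Handling of loss (Analyses).** "Missing data at follow-up will be imputed using regression imputation". The predictors in that regression are not listed.
- **Check on selection (Analyses and Discussion).** The non-response analysis sets included participants against all children aged 5–16 reported to the seven centers during recruitment. It uses age, gender, ethnicity, living situation, type of maltreatment and outcome of the AMK procedure. The Discussion attaches it to the first limitation, recruitment: "In addition, a non-response analysis will be performed to examine the presence of this possible selection bias". The second limitation, loss to follow-up, gets no analytic response.

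Retention measures are several forms of contact information, an email or letter, a visit to the last known address (Recruitment and sample size), and vouchers or presents plus help with the questionnaire (Assessment).

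**The concern.** The main objective is the course of mental health and quality of life over 1.5 years. At the last assessment about two outcomes in five would be imputed rather than measured.

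Regression imputation gives a lost child the score predicted from children who stayed and had the same observed values. That is sound when the observed values account for dropout. It is not sound when a family leaves because of something that arose after its last completed questionnaire and that also changed the child's score. One of the article's two stated reasons could be of that kind.

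The only selection check looks at who entered, so it cannot show whether those who left differed from those who stayed. The tracing measures address lost contact, and the vouchers and assistance are general. None is aimed at families who leave because of new problems.

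At stake is whether a reported improvement, or a reported absence of deterioration, describes the whole cohort or mainly the families that remained. A more careful imputation procedure, such as multiple imputation, would improve the standard errors but would not remove this bias.

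**Working it through.** **Step 1. The plan's own figure.** Inputs: 150 dyads at the last assessment and 40% loss after baseline, both from Recruitment and sample size. Implied baseline = 150 / (1 − 0.40) = 250, so 250 − 150 = 100 final outcomes are missing. No baseline number is stated, so this is a back-calculation and not an independent check. It takes the 40% as cumulative and leaves aside dyads excluded because maltreatment is not confirmed.

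**Step 2. Bias formula.** Let p be the share of all dyads lost because of new problems, and delta the amount, in SD, by which their true mean at 1.5 years is worse than their imputed mean. Other losses are taken to be explained by observed data. Then

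bias in the mean at 1.5 years = p x delta, with p at most 0.40.

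Delta and p are assumptions; the article gives neither.

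| delta (SD) | p = 0.40 (all losses) | p = 0.20 (half of losses) |
|---|---|---|
| 0 | 0 | 0 |
| 0.2 | 0.08 | 0.04 |
| 0.5 | 0.20 | 0.10 |

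**Step 3. Scale.** Assume an SD of change of 0.9. With 150 observed dyads the standard error of mean change is 0.9 / √150 = 0.0735 SD.

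- p = 0.40: 0.08 / 0.0735 = 1.1 and 0.20 / 0.0735 = 2.7 standard errors.
- p = 0.20: 0.04 / 0.0735 = 0.5 and 0.10 / 0.0735 = 1.4 standard errors.

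**Step 4. Does the mechanism produce the bias?** A simulation used 250 children, four waves, 40% monotone dropout, deterministic sequential regression imputation from earlier waves, and 500 runs per scenario. Assumed: a true change of −0.30 SD in a problem score (an improvement), and a within-child correlation of 0.4, 0.6 or 0.8.

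| Dropout depends on | Bias in change (SD), over the three correlations |
|---|---|
| nothing | −0.004 to +0.003 |
| the previous, observed score | −0.007 to −0.003 |
| the current, unseen score, log-odds +0.5 per SD | −0.083 to −0.044 |
| the current, unseen score, log-odds +1.0 per SD | −0.168 to −0.082 |
| the current, unseen score, log-odds −0.5 per SD | +0.038 to +0.085 |

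A negative bias means that the course looks too favourable. When worse unseen scores drive dropout, the true −0.30 is estimated at about −0.34 to −0.47. When dropout follows observed scores, imputation from earlier waves works. When better-off children leave, the sign reverses.

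**The case against.** The strongest case on the other side has five parts.

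1. **The article does not predict this dropout.** A reader might infer that the plan expects families to leave because of new problems. It does not: the wording is conditional, mobility is named as well, and only the 40% total is an expectation. This stands.

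2. **The direction is not established.** A reader might infer that the course will look better than it is. That needs the new family problems to worsen the child's score beyond what earlier data predict. The article speaks of family problems and says nothing about the child's later score. The simulation gives no material bias if observed data explain dropout, and the opposite bias if the dependence is reversed. This stands.

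3. **The mechanism may be partly observed.** Being a multi-problem family predates follow-up, and the study records parental stress, life events, living situation, financial problems and alcohol use. If these enter the imputation regression, delta shrinks. This stands in part: the article does not say that they enter, and problems that begin after the last questionnaire would still be missed.

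4. **Retention goes beyond contact details.** It would be wrong to say that contact details are the only safeguard, given letters, tracing visits, vouchers and assistance. This stands. It remains true that none is directed at families who leave because of new problems.

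5. **Attrition tables and sensitivity analyses usually belong in a fuller plan that is not shown.** Their absence alone would be no finding. But the article does more than leave the matter open: it commits to an imputation method, defines its selection check as one at entry, and names a reason for loss that the method covers only under a condition it does not discuss.

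**Conclusion.** The point holds as a mismatch between a stated method and a stated possible cause of dropout, at a level of loss where it matters for the main objective. If new problems drive dropout and also worsen the child's unseen score, the 1.5-year course may look too favourable by p x delta, at most 0.40 x delta. That is 0.08 SD at delta 0.2 and 0.20 SD at delta 0.5 if every loss is of this kind, and less if only some are. The upper figure exceeds the largest simulated bias, 0.17 SD, so it is best read as an outer illustration.

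The 40% comes from the article. Delta, the split of losses by cause, the SD of change and the strength of dependence are all assumptions, and the documents fix neither the size nor the sign of the bias.

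A reader might go further and conclude that the imputation would make AMK involvement appear beneficial. The documents do not support that: the objective is to describe the course, and any causal reading of a cohort without a comparison group would be doubtful whatever the imputation.

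The change should be made. It concerns the main result and costs little, and its importance cannot be judged without the comparison proposed below.

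**What to change.** In the Analyses section:

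1. **Extend the non-response analysis to dropout.** At each wave, compare lost with retained dyads on T0 and last observed CBCL and PedsQL, parental stress, living situation, ethnicity and AMK outcome. Include the variables that predict loss, together with earlier outcome values, in the imputation model. This reduces the part of the bias that observed data can explain.
2. **Add a shift analysis for objective 1.** Repeat the analysis with dropouts' imputed values made worse over a range fixed in advance, for example 0.1 to 0.5 SD. Report the shift at which the conclusion on change over time reverses, and state the conclusion subject to that result. This covers the part that the first step cannot test, because the scores concerned are never seen.

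The cost is some wording and a few extra runs on data already collected, with no added visits or questionnaires. The downside is that the stated conclusion may become less firm.
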